### Study outcomes

The primary outcome measure was time-to-disease progression (in days) among women with early-onset preeclampsia, defined as the interval from diagnosis to the first occurrence of a composite endpoint indicating clinical deterioration. Disease progression is defined as the development of any of the following: consistently elevated blood pressure of 160/110 mmHg or higher; severe proteinuria of 3+ or a urine protein/creatinine ratio of 0.3 or higher; platelet counts less than 100,000/µL; elevated liver enzymes (AST/ALT) or evidence of hepatic dysfunction; serum creatinine level greater than 1.1 mg/dL or doubling of baseline creatinine in the absence of other renal diseases; symptoms and signs of pulmonary oedema such as dyspnoea and crackles on lung auscultation; cerebral or visual disturbances such as headaches, visual disturbances, altered mental status, seizures (eclampsia), or other neurological symptoms; and evidence of placental dysfunction such as placental abruption, fetal growth restriction or oligohydramnios on ultrasound examination [2,5]. Participants who do not experience disease progression will be censored at delivery or at the end of follow-up. Secondary outcomes will include (1) safety and treatment tolerability, (2) maternal outcome (maternal mortality), and (3) composite neonatal outcomes, including low birth weight in term neonates (baby’s birth weight less than 2500g), IUGR, stillbirth, NICU admission, and perinatal and neonatal mortality. Women who develop preeclampsia with severe features will be managed as per the obstetric unit protocol and will be excluded from further participation in the study.

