### Sample size calculation

The sample size was calculated assuming a 1:1 randomization ratio, a two-sided type I error rate (α) of 0.05, and 80% statistical power to detect a hazard ratio of 0.5 between the NAC and placebo groups, based on an estimated 33.3% baseline probability of disease progression among pregnant women with early-onset preeclampsia [24]. Allowing for an anticipated 15% loss to follow-up or missing outcome data, the total planned sample size is 153 participants, who will be randomly allocated in equal proportions to the two study arms (approximately 76–77 participants per group).

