### Data management and statistical considerations

Data will be collected prospectively with continuous data entry and checking. Queries will be actively pursued to ensure prompt clarification. Data will be entered into the REDCap database and then exported to Stata version 18.0 for Windows (StataCorp LLC, Texas, USA) for statistical analyses. Missing or incomplete data will be handled by running a missing values analysis using pairwise or listwise deletion if no pattern is detected or the multiple imputation method if a pattern is detected [26]. The primary analysis will be conducted on an intention-to-treat basis. The effectiveness of blinding will be evaluated using descriptive statistics and by comparing the proportion of correct guesses between study arms using the Chi-square test. Kaplan-Meier estimates with a Log-rank test will be used to calculate and compare the time-to-disease progression for the treatment groups while considering deliveries without preeclampsia with severe features as censored observations. We will then perform Cox proportional hazard models with a backwards conditional method to compare the study outcomes between the treatment arms while adjusting for other covariates using hazard ratios (HRs) and 95% confidence intervals (95%CIs). We will assess the calibration or goodness-of-fit statistic of the final model using the Hosmer-Lemeshow test, while the model’s explanatory power will be reported with Nagelkerke’s pseudo-R². Subgroup analyses will also be performed to assess the differential effects of significant covariates on the impact of NAC on disease progression. With oversight from the DSMC, two interim analyses of efficacy and futility for the primary outcome (progression to severe disease) will be conducted at 50% and 75% enrolment using O’Brien-Fleming stopping criteria [27] at cutoff *p*-values of less than 0.013 and 0.025, respectively

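### The interim looks are timed by enrolment while the log-rank test's information is events, so fixed O'Brien-Fleming cut-offs fall at an uncontrolled and on average slightly smaller information fraction

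*Protocol article*

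**What the plan says.** The section Data management and statistical considerations names the primary test: "Kaplan-Meier estimates with a Log-rank test will be used to calculate and compare the time-to-disease progression". In the same paragraph it says that "two interim analyses of efficacy and futility for the primary outcome (progression to severe disease) will be conducted at 50% and 75% enrolment", under O'Brien-Fleming criteria, with cut-off p-values of "less than 0.013 and 0.025, respectively". With 153 women, the looks come after about 76 and 115 randomisations.

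The Sample size calculation section is also in time-to-event terms: "a two-sided type I error rate (α) of 0.05, and 80% statistical power to detect a hazard ratio of 0.5", "assuming a 1:1 randomization ratio", and an "estimated 33.3% baseline probability of disease progression", with a 15% allowance for loss. Under Study outcomes, "Participants who do not experience disease progression will be censored at delivery or at the end of follow-up". The article gives no event count for either look or for the final analysis, and no rule that links the cut-offs to the events observed.

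**The concern.** O'Brien-Fleming boundaries are functions of the information fraction. For a log-rank test that fraction is, to a close approximation, the events seen so far divided by the events at the final analysis. When half the women have been enrolled, the most recently randomised are still pregnant and at risk and have contributed little. The event fraction is therefore below one half on average, and its value in the actual trial is left to chance.

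A cut-off fixed in advance for 50% is then applied at some other fraction. This holds for any fixed cut-off, so correcting the two printed values would not remove it. At stake are the match between the error spent and the information available, and the number of events behind a decision to stop for efficacy or futility.

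**Working it through.** **Inputs from the article.** N = 153, 1:1 allocation; placebo progression 33.3%; hazard ratio 0.5; two-sided alpha 0.05; power 80%; loss 15%; entry at 24 to 34 weeks; enrolment April 2026 to December 2027.

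**Assumed, because the article does not give them.** Uniform accrual over about 89 weeks; uniform gestational age at entry; constant hazard calibrated to 33.3% on placebo; follow-up ending at 34.5 to 38 weeks; lost women contribute no events.

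**Step 1. Expected events.** Under proportional hazards the NAC probability is 1 − (1 − 0.333)^0.5 = 0.183. The average over the arms is (0.333 + 0.183)/2 = 0.258.
- Final, after 15% loss: 153 × 0.258 × 0.85 = 33.6. Without loss: 153 × 0.258 = 39.5.
- First look, if the first half were fully followed: 0.5 × 33.6 = 16.8. This is exactly half of 33.6, so a count of about 17 does not by itself show a fraction below 50%. The shortfall comes from incomplete follow-up.

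**Step 2. Follow-up lag.** I simulated 4,000 trials per scenario, with looks at the 76th and 115th randomisation and accrual over 89 weeks:

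| Follow-up ends (weeks) | Events at look 1 | Events at look 2 | Final events | Fraction 1 | Fraction 2 |
|---|---|---|---|---|---|
| 34.5 | 15.4 | 24.1 | 33.9 | 0.455 | 0.709 |
| 36 | 15.1 | 23.7 | 33.7 | 0.448 | 0.704 |
| 37 | 15.1 | 23.7 | 33.9 | 0.444 | 0.699 |
| 38 | 14.8 | 23.4 | 33.7 | 0.438 | 0.693 |

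The first-look count has a 5th to 95th percentile of about 9 or 10 to 21. The first-look fraction in single trials runs from about 0.32 to 0.59. With no loss and follow-up to 37 weeks the first look has 17.7 events and the fraction is still 0.443. If accrual took only 52 weeks, the mean fractions would be about 0.39 to 0.43 and 0.64 to 0.69.

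**Step 3. What the boundary should do over that range.** Lan-DeMets O'Brien-Fleming-type spending, with 0.025 per side, has cumulative two-sided value 4 × [1 − Φ(2.241/√t)]:
- t = 0.32: 0.00015
- t = 0.45: 0.0017
- t = 0.50: 0.0031
- t = 0.59: 0.0070

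No single fixed cut-off suits all of these.

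**Step 4. Type I error from the timing alone.** I took cut-offs that are correct for fractions 0.50/0.75/1 and applied them at other fractions:

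| Actual fractions | Classic (0.0042, 0.0194, 0.0430) | Lan-DeMets (0.0031, 0.0183, 0.0440) |
|---|---|---|
| 0.50/0.75 | 5.0% | 5.0% |
| 0.45/0.70 | 5.1% | 5.1% |
| 0.35/0.60 | 5.4% | 5.4% |

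With the printed 0.013 and 0.025 and a final test at 0.05 (assumed), overall alpha is about 6.3% at 0.50/0.75 and about 6.4% to 6.5% at 0.45/0.70. Most of that excess belongs to the cut-off values.

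**The case against.** The strongest reply is that the timing error is small. Follow-up lasts weeks and accrual about 20 months, so enrolment tracks events closely. If primary-endpoint assessment stops at 34 weeks, as the marks in Table 1 suggest, the fractions are about 0.47 and 0.72. That reply stands, and it limits the point to a modest one.

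A reader might infer much more, in two ways that the documents do not support as consequences of the enrolment trigger.

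- **Looks at 26% and 39% information.** A hazard ratio of 0.5 with 80% power needs 4 × (1.960 + 0.842)²/(ln 0.5)² = 65.3, so 66 events; 17/66 = 26% and 26/66 = 39%. But a trial of 153 women expects only about 34 to 40 events on its own inputs, and that is the relevant denominator. The gap to 66 is a sample-size fault.
- **Stopping on a grossly exaggerated effect.** With 17 events, p < 0.013 needs a hazard ratio of at most exp(−2 × 2.484/√17) = 0.30. If the true value is 0.5, trials that stop there report about 0.23 on average (geometric mean). An exact 50% event trigger (18.5 of 37 events) with the same cut-off gives 0.315 and 0.25. Nearly all of the exaggeration comes from the low event count and the 0.013 cut-off.

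It can also be said that data-cut rules commonly sit in an analysis plan or monitoring charter that is not shown. That is fair for the data cut. It does not cover the trigger and the cut-offs, which the article itself fixes.

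**Conclusion.** The point holds as a cheap improvement, not as a serious threat to validity. The article times the looks by enrolment and fixes the cut-offs in advance, for a test whose information is events. On its stated inputs the looks fall on average at about 45% and 70% of final events instead of 50% and 75%. The first rests on about 15 to 17 events, and its fraction in a single trial could lie anywhere from about 0.32 to 0.59.

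The timing alone moves overall type I error from 5.0% to about 5.1%, or to about 5.4% in a less favourable case. The fractions rest on assumed accrual, entry and delivery timing. That the fraction is uncontrolled does not depend on those assumptions. The printed cut-off values and the shortfall of events against the 80% power claim are separate faults and should be judged separately.

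**What to change.** In Data management and statistical considerations, choose one of two routes:

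1. Define the looks as 50% and 75% of a stated number of primary-outcome events. The number must be one that 153 women are expected to yield, about 34 to 40 on the stated inputs. That puts the looks at about 17 to 20 and 26 to 30 events. A target of 66 would not work: 75% of it is about 50 events, more than the trial expects in total.
2. Keep the looks at 50% and 75% enrolment.

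In either case, compute each boundary by Lan-DeMets O'Brien-Fleming-type spending at the event fraction observed at the data cut, and let the final boundary spend the remaining alpha at the actual final event count. Put the same wording in the monitoring committee's charter.

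**Cost.** A sentence or two of text, while recruitment has not begun, and no extra women for the re-timing itself. Under the first route the dates of the looks are less predictable and the second may fall near the end of enrolment. The first boundary becomes stricter, about 0.0017 at a fraction of 0.45 or 0.0031 at 0.50 against the printed 0.013, so early stopping for benefit is rarer. The change does not cure exaggeration among trials that do stop: at 18.5 events and p of about 0.0031, crossing needs a hazard ratio of about 0.25 or less.

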**Methods:**

This is the study protocol for a proof-of-concept, double-blind, randomized, controlled trial to be conducted between April 2026 to July 2028 at the maternity units of the two teaching hospitals in Lagos, Nigeria. At baseline, n = 153 sexually active women aged 18 years or older diagnosed with early-onset preeclampsia at 24–34 weeks’ gestation will be randomised to receive either daily oral tablet containing 600 mg of NAC or a placebo tablet that is matched for appearance and the dosing regimen in addition to standard antenatal care from diagnosis (randomisation) until either 34 weeks’ gestation or delivery, whichever comes first. The primary endpoint is the time-to-progression (in days) of early-onset preeclampsia to severe disease. The data analysis will be conducted on an intention-to-treat basis. Kaplan-Meier estimates with a Log-rank test will be used to calculate and compare the time-to-disease progression for the treatment groups, while Cox proportional hazard models with a backwards conditional method will be used to compare the primary endpoint between the treatment arms while adjusting for other covariates for precision using hazard ratios (HRs) and 95% confidence intervals (95%CIs). Subgroup analyses will also be performed to assess the differential effects of significant covariates on the impact of NAC on disease progression. Statistical significance will be reported as *P* < 0.05.

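### The interim cut-offs of 0.013 and 0.025 are not O'Brien-Fleming levels, and with the only significance level the protocol states (0.05) the overall two-sided error is about 6.3%, not 5%

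*Protocol article*

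**What the plan says.** Under Data management and statistical considerations, the protocol article states that "two interim analyses of efficacy and futility for the primary outcome (progression to severe disease) will be conducted at 50% and 75% enrolment". It names O'Brien-Fleming as the method and prints the "stopping criteria [27] at cutoff *p*-values of less than 0.013 and 0.025, respectively".

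The Sample size calculation section sets "a two-sided type I error rate (α) of 0.05, and 80% statistical power to detect a hazard ratio of 0.5". The only other significance level is in the Methods part of the abstract: "Statistical significance will be reported as *P* < 0.05". No separate nominal level is given for the final analysis of the primary outcome.

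The primary comparison is a log-rank test of time to progression, so statistical information accrues with events, whereas the looks are timed by enrolment.

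**The concern.** The O'Brien-Fleming design makes early stopping hard: it spends very little alpha at the first look and leaves the final test close to the full level. A first cut-off of 0.013 at half the information does not have that shape. The named method and the printed numbers therefore give the monitoring committee different instructions. A p-value of 0.010 at the first look crosses the printed cut-off but not an O'Brien-Fleming boundary.

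Two more lenient looks followed by a test at 0.05 also use more than the 5% on which the design rests. At stake are both the decision to stop early for efficacy and the claim of significance at the end.

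**Working it through.** **Inputs.** From the protocol: overall two-sided alpha 0.05; looks at 50% and 75% plus a final analysis; interim cut-offs 0.013 and 0.025; stated significance level 0.05. Assumptions: the p-values are two-sided, the information fraction equals the enrolment fraction (relaxed in step 4), and no binding futility rule applies.

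**1. What O'Brien-Fleming gives at t = 0.50, 0.75, 1.**

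- Classical: reject when |Z| exceeds c/√t. Solving for 5% overall gives c = 2.024. The limits are 2.024/√0.50 = 2.863, 2.024/√0.75 = 2.337 and 2.024.
- Lan-DeMets O'Brien-Fleming-type: cumulative alpha spent is 4{1 − Φ(2.2414/√t)}, that is 0.00305, 0.0193 and 0.05.
- A more lenient version that applies the spending function once to the whole 0.05, in place of 0.025 per side, was also tried.

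| Nominal two-sided p | 50% | 75% | 100% |
|---|---|---|---|
| Protocol | 0.013 | 0.025 | 0.05 (only level stated) |
| Lan-DeMets, 0.025 per side | 0.0031 | 0.0183 | 0.0440 |
| Classical | 0.0042 | 0.0194 | 0.0430 |
| Lan-DeMets, single 0.05 | 0.0056 | 0.0216 | 0.0411 |

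The protocol's pair is not reproduced by any of these. At the first look, 0.013/0.0031 = 4.2, 0.013/0.0042 = 3.1 and 0.013/0.0056 = 2.3. At the second, 0.025 exceeds all three.

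**2. Overall error of the rule as printed.** Under the null the three Z statistics are standard normal with correlation √(t_j/t_k), that is 0.816, 0.707 and 0.866. The limits are 2.484 (p = 0.013), 2.241 (0.025) and 1.960 (0.05). Numerical recursion gives the probability of first crossing at each look:

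- first look: 0.01300
- second look: 0.01815 (0.03115 spent by then)
- final look: 0.03144
- total: 0.06259

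A Monte Carlo check with 4 million draws gave 0.0627.

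**3. Other final levels with 0.013 and 0.025 kept.**

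- Final level 0.044: 0.03115 + 0.02651 = 0.0577.
- To hold 5%, the final look may add only 0.05 − 0.03115 = 0.01885, which corresponds to a final level of about 0.034.

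Conversely, correct Lan-DeMets interim levels (0.0031, 0.0183) followed by a final test at 0.05 give 0.0554, and correct classical ones 0.0562. Both the interim and the final levels need attention.

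**4. Events lagging enrolment.** The Trial status section puts enrolment between April 2026 and December 2027, about 89 weeks. With uniform accrual and a mean lag of 4.5 weeks from enrolment to event (both assumed), each fraction falls by about 4.5/89 = 0.05, to 0.45 and 0.70. The printed rule then gives 0.0644, while the Lan-DeMets levels become about 0.0017, 0.0142 and 0.0454. So the correct cut-offs depend on the event fraction actually reached.

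**5. Power cost.** Take a single-look design with exactly 80% power (drift 1.960 + 0.842 = 2.802, mean of Z at fraction t equal to 2.802√t). In 2 million simulated paths the Lan-DeMets levels gave 79.2%; keeping 0.013 and 0.025 with a final 0.034 gave 77.4%. These are relative figures and do not assess whether 153 women provide 80% power.

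**The case against.** The strongest objection is that the final level is inferred. The statistical section prints interim cut-offs only; the 0.05 comes from a general reporting sentence in the abstract and from the design alpha, which is an overall rate. A reduced final level may stand in an analysis plan or committee charter that is not shown. The pair also lies near a Wang-Tsiatis boundary with shape 0.25 (0.0124, 0.0239, 0.0355), so it may come from a valid design. This stands in part: the 6.3% is conditional on a final test at 0.05. It does not rescue the printed figures. They are wrong for the named method whatever the final level is, and a usual O'Brien-Fleming final level of 0.044 would still leave about 5.8%.

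A reader might infer several stronger points that the documents do not support:

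- **An error as high as 6.8%.** That needs event fractions near 0.33 and 0.60. On the accrual assumption above, these imply mean lags of about (0.50 − 0.33) × 89 = 15 and (0.75 − 0.60) × 89 = 13 weeks. Treatment, and primary-endpoint assessment in Table 1, run from 24 to 34 weeks' gestation, at most about 10 weeks. Follow-up continues to delivery, but a mean lag that long is hard to reconcile with this timetable.
- **At most about 17 events at the first look.** This takes 130 evaluable women (153 × 0.85) with a true hazard ratio of 0.5. Under the null the same inputs give 130 × 0.333 = 43 events, or about 22 at half. It is not a maximum.
- **An exaggerated hazard ratio peculiar to this rule.** Any early efficacy stop on few events tends to overstate the effect. A stricter boundary makes such stops rarer, but the estimate needed to cross is more extreme.
- **That the efficacy cut-offs are also the futility rule.** The sentence is compressed and can be read otherwise; a futility criterion may be held elsewhere.

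**Conclusion.** The point holds. The cut-offs do not belong to the boundary that the protocol names: about 0.003 to 0.006 would be expected in place of 0.013, and 0.018 to 0.022 in place of 0.025, across the variants tried. This part depends only on two-sided testing and on looks at half and three quarters of the information. A one-sided reading of the interim cut-offs would make matters worse (8.3% overall with a final two-sided 0.05).

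The breach of the 5% error rate is conditional on the final level. At the stated 0.05 the overall error is about 6.3%, an excess of about 1.3 percentage points; at 0.044 it is about 5.8%; only at about 0.034 does it return to 5%. A modest lag of events behind enrolment raises the first figure to about 6.4%. A binding futility rule would lower it somewhat, but none is stated.

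**What to change.** Choose one consistent set of levels and state it before the first look:

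- **Preferred.** Replace 0.013 and 0.025 with levels from a Lan-DeMets O'Brien-Fleming-type spending function, evaluated at the observed event fraction at each look. If the looks fall at 50% and 75% of the information, these are about 0.003 and 0.018. State the matching final level for the primary test, about 0.044 in that case, in place of P < 0.05.
- **Alternative.** Keep 0.013 and 0.025, drop the O'Brien-Fleming label and test the final analysis at about 0.034. These figures hold for information fractions of 0.50 and 0.75.

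In either case, add that these p-values govern efficacy only.

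The change is to wording in the protocol and any monitoring charter; recruitment had not begun when the article was submitted. The price is a stricter final threshold: by the calculation above, about 0.8 of a percentage point of power for the preferred option (80.0% − 79.2%) and about 2.6 points for the alternative (80.0% − 77.4%). The spending approach needs a planned total number of events from which to compute the fraction. The protocol article does not give one, so it would have to be stated too. Looks may still be scheduled by enrolment, provided the levels are computed from the events observed.

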### Ethical considerations

Approval for the trial was obtained from the research ethics committee of the Lagos University Teaching Hospital (LUTH-HREC – ADM/DSCST/HREC/APP/8031; February 27, 2026) and the permission of the Lagos State Health Service Commission (LSHC/2222/VOLIV/99; March 13, 2026). The trial will be conducted in accordance with the Declaration of Helsinki. Participants will be informed about the study objectives, procedures, potential risks and benefits, and their right to withdraw at any time without any consequences to their care. Written informed consent will be obtained by the study investigators or trained clinical research assistants from all participants prior to enrolment. All data collected will be treated with strict confidentiality and used solely for this research. The trial and statistical analysis will be conducted with fidelity, and the reporting will adhere to the guidelines outlined in the Standard Protocol Items: Recommendations for Interventional Trials (SPIRIT) checklist. Clear and comprehensive standard operating procedures (SOPs) for participants’ treatment administration, data collection, follow-up evaluations, adverse event management and statistical analyses will be developed to align with the trial protocol. The study team will also conduct regular monitoring to ensure adherence to these SOPs. An independent data and safety monitoring committee (DSMC) will also review the interim analyses to ensure the robustness of the data, treatment safety, and adherence to the trial protocol.

